#### Materials and procedure

The online survey will be hosted on Qualtrics (2018) [38] and consist of nine open questions and three closed questions. Prior to answering these questions, patients will be presented with an information sheet, consent form and demographic questionnaire. Consent will be gained via ticking boxes on Qualtrics (2018) [38], and the survey should take approximately 10 min to be completed, determined through piloting by the research team.

### Staff online survey

As well as focus groups, an online survey will be distributed to staff. Focus groups capture collective views and group interactions. However, organ donation is a personal topic and some staff may prefer to express opinions privately than in a group. An online survey will help elicit as many views of the intervention in terms of feasibility as possible.

#### Participants and recruitment

Following completion of the focus groups, an online survey will be distributed to all trained staff members. No incentives will be used to recruit staff; however, a reminder email will be sent approximately 2 weeks following the first email. A final reminder email, with the same content, will be sent at 4 weeks following the first email. Staff will be informed that this survey aims to capture any experiences or views that they do not feel comfortable sharing in the focus groups or anything they forgot to mention during the focus group.

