*Yes – Selected Organs (prompt will be turned off)*
i.
*Yes - Heart*
ii.
*Yes - Liver*
iii.
*Yes - Kidneys*
iv.
*Yes - Corneas*
v.
*Yes - Lungs*
vi.
*Yes - Pancreas*

*Unsure - Patient will think about it (prompt will appear again at next appointment)*

*Do not ask patient again (prompt will be turned off)*

*Patient believes they are already on the register (prompt will be turned off)*
i.
*Would the patient like to re-register?*

*Yes - All organs and Tissues*

*Yes - Selected organs and Tissues*
i.
*Yes - Heart*
ii.
*Yes - Liver*
iii.
*Yes - Kidneys*
iv.
*Yes - Corneas*
v.
*Yes - Lungs*
vi.
*Yes - Pancreas*

*No - Patient would not like to re-register*

f.
*Patient was not asked*
i.
*Not appropriate for consultation*
ii.
*Lack of time*
iii.
*Clinician personal beliefs (only select if personal view of clinician NOT situational factor)*
iv.
*Other reason, please specify*

If staff member presses ‘No’ on the prompt, this indicates they have not or will not ask the patient to join the NHS ODR. They will then be instructed to complete the following questionnaire which records reason why the patient was not asked.g.
*Patient was not asked. Reason why patient was not asked:*
i.
*Not appropriate for consultation*
ii.
*Lack of time*
iii.
*Clinician personal beliefs (only select if personal view of clinician prevents patient being asked)*
iv.
*Other reason, please specify*

It was highlighted that staff may select the ‘Yes’ questionnaire at the beginning of a consultation but be unable to carry out prompted choice as the consultation progresses. To allow staff to record that the patient was not asked under these circumstances question f. was included in both the ‘Yes’ and ‘No’ questionnaire.

To ensure no untrained staff ask patients about organ donation, the prompt will only appear for staff who have received the training and only for patients aged 18 or over. If prompted choice has previously been completed for the patient and the patient responded “Yes”, “Do not ask patient again” or “Patient believes they are already on the register”, the prompt will switch off and the patient will not be asked again at subsequent appointments.

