### Monitoring

During the 3-month prompted choice period, the intervention will be monitored weekly by the research team. This will include an examination of raw data from SystmONE to ensure no staff member without training has conducted prompted choice, restocking leaflets and ensuring all informative posters are still in place. If it is found that an untrained staff member has asked a patient the question, due to computer error, the investigator will inform them verbally that they should not be doing this and aim to amend the prompt on SystmONE.

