### Data collection, management and analysis

Data will be collected in four ways: registration data via the practice computer system, a training evaluation survey, focus groups with staff and patients and an online survey with participating staff.

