### Training evaluation survey

To examine staff reaction to the training, a qualitative and quantitative paper survey will be distributed directly after it has been delivered. Participants will be provided with an information sheet, consent form (referring to the training evaluation survey only) and training evaluation form. Confidentiality, anonymity, the voluntary nature of the survey and the right to withdraw will be highlighted to participants prior to them completing the consent forms. The evaluation form will quantitatively assess overall views of the session, how prepared the staff feel to conduct the prompted choice element and answer questions about organ donation, the acceptability of the training content, presentation style and use of resources. Qualitative open questions will be asked concerning strengths, weaknesses and potential improvements to the training session.

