### Staff focus groups

#### Participants and recruitment

Following completion of the prompted choice period, participating staff will be invited to take part in qualitative focus groups. Each focus group will contain 6–10 participants and will be split according to staff group (clinical GP, clinical non-GP and administrative). Staff will be invited via email and an information sheet will be attached. The focus groups will take place for 1 h, during the 2-h (12 pm–2 pm) staff lunch break to minimise the impact on the running of the practice, with lunch provided for staff by the research team. To ensure staff are able to attend the focus groups, these will be organised to maximise staff availability.

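### Any clinician who declines or misses the training has no stated route to give reasons or views, so staff themes on non-uptake are likely to be under-represented

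*Protocol article*

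**What the plan says.** The recruitment paragraph under Staff online survey states that once the focus groups are finished "an online survey will be distributed to all trained staff members". The opening of Data collection, management and analysis describes the same instrument as "an online survey with participating staff".

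The other staff sources are defined as follows:

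- **Training evaluation survey:** "a qualitative and quantitative paper survey will be distributed directly after it has been delivered", that is, to those who were at the session.
- **SystmONE record:** under Prompted choice, "the prompt will only appear for staff who have received the training". The coded reasons for not asking a patient are entered through that prompt.
- **Staff focus groups:** "participating staff will be invited to take part in qualitative focus groups", in separate GP, other clinical and administrative groups. The article does not define participating.

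The introduction to the staff survey gives its purpose: "An online survey will help elicit as many views of the intervention in terms of feasibility as possible". The Rationale frames the question as one about practice staff and patients at large, under the resource pressures of UK general practice.

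**The concern.** In a feasibility study of an intervention that depends on staff being trained first, failure to get trained is itself a feasibility result. The Background names time constraints, lack of practice resources and barriers to access as the difficulties met in earlier UK work. A clinician who cannot find time for the session, or who objects to raising organ donation in a consultation, shows these difficulties at the earliest step. As the plan is written, that person drops out of view there, because each staff source starts from training or participation.

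The findings are to inform a multi-practice feasibility cluster trial. If reasons for not training are not collected in this practice while the study is live, they will be hard to recover later, and the next study will be planned mainly on the experience of those who were trained.

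**Working it through.** There is no sample size, error rate or stated figure to reproduce; the article says that no sample size calculation was done. The check is to set the eligibility for each staff source beside the question the study asks.

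**Step 1. Who can be heard, by source.**

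| Source | Who is eligible | Trained, never asked a patient | Never trained |
|---|---|---|---|
| Training evaluation | Those at the session | Yes | No |
| SystmONE reasons for not asking | Staff who see the prompt, so trained staff | Yes | No |
| Focus groups | Participating staff (undefined) | Probably | Not stated |
| Staff online survey | Trained staff | Yes | No |

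The last column has no clear yes. The one uncertain entry is the focus groups, because participating is not defined and an administrative group is included.

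**Step 2. Does the article expect untrained staff?** It allows for them. Prompted choice is to be offered by clinical staff who have received training, the prompt is switched on only for those staff, and Monitoring sets out what happens "If it is found that an untrained staff member has asked a patient the question". In Table 1, staff training is marked only in the enrolment column, before April 2018, so no later session is shown for someone who was absent. The article does not say how many staff will be untrained, and it may be none.

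**Step 3. What is the target?** The Rationale asks about acceptability to practice staff, and the survey's stated purpose is to gather as many views as it can. Neither is confined to trained staff.

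**Step 4. Can a size be given?** If a share of staff finding the intervention acceptable were being estimated, the overstatement would be

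(number untrained / all staff) × (share accepting among trained − share accepting among untrained).

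Only one term is documented: 30 staff, under Study setting. The number untrained and both shares are missing. The expression is zero if nobody is untrained or if the two groups hold the same views. Its sign is positive only if untrained staff are less favourable, which is plausible but not shown.

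The formula also describes a quantity the study does not plan to report. The staff survey has 13 open questions, and the qualitative data go to framework analysis for themes. The quantitative staff ratings described are in the training evaluation, and they concern the session and how prepared staff feel. The practical loss is therefore missing or thin themes, and no percentage should be attached to it.

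**The case against.** The strongest reply is that the plan already takes pains to record reluctance. A trained clinician who never puts the question still receives the survey and two reminders. Lack of time, personal beliefs and a free-text reason can be coded at the prompt, and the Distress section says that conversations avoided for that reason will be recorded. All of this stands. A reader might infer that only staff who trained and then took part are heard; the documents do not support that, and the gap is confined to staff who were never trained.

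A reader might also infer that staff acceptability will be overstated by a definite number of percentage points. That fails for the reasons in Step 4. Nor can the 30 staff be read as 30 potential refusers: the total includes administrative staff, prompted choice is for clinical staff, and the article does not give the number of clinicians.

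A third tempting inference is that the survey invitation shuts out those who skipped the focus groups. It says the survey is for views people were not comfortable sharing there or forgot to mention. The first part can cover someone who stayed away from the group for that reason, so the wording is imperfect rather than excluding.

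Finally, it is defensible to ask for views of an intervention from those who delivered it, and a journal article may leave the reporting of training uptake to the full protocol. The absence of an uptake figure is accordingly not counted as a fault. What remains is that the article does state the survey's recipients, and that rule leaves out the staff best placed to explain non-uptake.

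**Conclusion.** The point holds in a limited, conditional form. The survey is restricted to trained staff, the other staff sources are restricted to trained or participating staff, and no route is stated for a clinician who declined or could not attend training. If any clinical staff remain untrained, reasons for non-uptake are likely to be under-represented and staff acceptability is likely to look more favourable than it is.

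This rests on two assumptions: that some clinical staff will be untrained, and that they are on the whole less favourable or more pressed for time than those who trained. The first is allowed for in the article but not quantified; the second is a reasonable expectation, not a documented fact. If either fails, little or nothing is lost. The change is worth making because it costs almost nothing and bears directly on the study's own question.

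**What to change.** 1. Send the existing staff online survey to all 30 staff rather than to trained staff only.
2. Open it with an item on training status. Route untrained staff to two or three short questions: why they were not trained, and how acceptable they find the intervention in their practice.
3. Word the invitation so that it does not presume the recipient attended a focus group.
4. Report how many eligible clinical staff were trained and how many were not, and present the themes by training status. Framework analysis is already to compare themes by participant group, so this adds one split.
5. Define participating staff for the focus groups, and use the same term for the survey in both places where its recipients are described.

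The cost is a few extra emails, the branched questions and a minor amendment. No extra visits or staff are needed. If everyone turns out to be trained, the survey runs as planned and full uptake is documented.

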#### Materials and procedure

The online survey will be qualitative and consist of 13 open questions. Prior to answering these questions, staff will be presented with an information sheet and consent form. Consent will be gained via ticking boxes on Qualtrics and the survey should take approximately 10 min.

### Data management

Data will be accessed through SystmONE at the practice by the investigator. Only data relevant to the study (i.e. the data specified in Table 2) will be accessed. Data will be anonymised by the investigator and exported from SystmONE for analysis on an encrypted memory stick. Paper consent forms and training evaluation forms will be stored in a locked filing cabinet at the University of Bedfordshire with access only available to the investigator. These will be stored for 5 years. Online staff survey data will be securely hosted on Qualtrics, who adhere to the data protection act, the general data protection regulation and online data protection procedures. At no point will participants be asked their name, and the only identifiable data collected by Qualtrics will be participants IP address. This will be deleted in all data sets extracted for analysis.

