### Intervention

#### Prompted choice

All clinical staff members (general practitioners, nurses, healthcare assistants and other clinical professionals) working in the practice, who have received training, will aim ask patients during their consultation if they wish to join the NHS ODR. Only eligible patients should be asked based on the following criteria:Inclusion criteria:Patient must be aged 18 years or overPatient must have the capacity to consent2.Exclusion criteria:(c)Patient is under 18 years of age(d)Patient does not have the capacity to consent

Staff will use their professional discretion to determine the capacity to consent and whether it is appropriate to ask the patient the question. They will be trained to limit potential distress by not asking those patients they believe could become distressed due to the content of their consultation. If staff are in any doubt regarding potential distress, they are advised in training not to ask the patient.

A requirement by the NHS REC is that staff must inform the patient that the question is being asked as part of a research study, a scripted question is provided to guide staff. Staff will be prompted to ask the question and to record patient responses using SystmONE, the clinical data system the practice uses. The potential responses for NHS ODR registration are based on the GMS1 form which is completed by new patients to a GP practice. The process of prompting staff and recording patient responses is described below.

Prompt Text.

*“Organ Donation Study.*

*If you will ask the patient to join the NHS ODR please press Yes.*

*If you will not ask the patient to join the NHS ODR please press No.*

*If you would like to ask the patient after the consultation, please press Pause.*

*When you are ready to ask please press ‘Save’ then ‘Resume Protocol’ or ‘Patient -> Resume’.*

*Please do not press the red x.”*

If staff member presses ‘Yes’ on the prompt, this indicates they have or will ask the patient to join the NHS ODR. They will then be instructed to complete the following questionnaire.

*“Eligibility*

*Does the patient have capacity to consent?*

*Yes*

*No (Staff member will be unable to complete the questionnaire if they answer no to this question)*

*Tell the following to the patient:*

*“As part of a research study, I am going to ask you some questions about organ donation.”*
2)
*Patient preferences on joining NHS ODR:*

*Yes – Any of organs and tissues (prompt will be turned off)*

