### Registration data

The data to be collected through SystmONE can be viewed in Table 2. Any leaflet registrations collected in the practice will be included in registration data analysis. However, it is possible that patients may register on the NHS ODR and post these forms themselves. Therefore, registration by leaflet data, collected at reception, will be treated with caution during analyses and interpretation.

**Table 2 Tab2:** Registration data to be collected by SystmONE

Variable	Response format
Registration type	SystmONE/Paper
Date of consultation	Dd/mm/yy
Patient age	Years
Patient ethnicity	ONS categories
Patient gender	Male or female
Patient asked	Yes/no
Reason patient not asked	Not appropriate/time/clinician personal beliefs/other (free text)
Patient joined NHS ODR	Yes/no/patient believes already on register
Organs selected	All/kidneys/heart/liver/corneas/lungs/pancreas
If no, which response	Unsure/do not ask again
Patient believes already on register. Re-register	Yes/no
Organs selected	All/kidneys/heart/liver/corneas/lungs/pancreas
Staff group	Doctor/Nurse/Healthcare Assistant

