## Discussion

Membership of the NHS ODR is the primary way to express organ donation wishes in the UK [1]. Interventions to target this are vital in reducing the discrepancy between the number of people donating their organs after death and those on the transplant list [1]. Currently, there is no location in the UK where people are routinely asked if they would like to join the NHS Organ Donor register. This study proposes general practice could be this location. However, the NHS is currently experiencing significant challenges [16]; therefore, an assessment of feasibility is essential before examining if this intervention would increase NHS ODR membership.

A limitation of this research is the lack of incentives for both the GP practice as a whole and for the individual participation of staff and patients in prompted choice. Introduced in 2004, the Quality Outcomes Framework (QOF) provides practices with financial reimbursement for each patient asked about a variety of health problems; for example smoking cessation [41]. Therefore, the lack of incentive in the current intervention may decrease the likelihood of staff completing the intervention form, including the elements concerning feasibility (e.g. reasons for not asking patients) and reduce the data captured using this method. Focus groups and online surveys could help examine the impact of this on the intervention; however, recruitment to these may also be impacted by the limited incentives (lunch for staff).

A key ethical concern when developing this research is the issue of distress to patients and staff during organ donation conversations. Predicting who might become distressed by the prompted choice conversation is challenging. To help ensure as minimal distress to patients occurs as possible, staff will be trained in how to best have these conversations by the experienced specialist organ donation nurse training division, a part of NHS Blood and Transplant. These staff have these conversations daily with grieving families and will help guide staff in this. Additionally, staff will be informed that they must use their professional judgement as to whether a conversation is appropriate for the patient they are about to see. If staff are unsure, they will be instructed to refrain from asking the question.

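### The permitted SystmONE data give no count of eligible prompts, so delivery of prompted choice can be described only among completed forms

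*Protocol article*

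**What the plan says.** The Objective section names fidelity beside feasibility and acceptability, and the Abstract lists registration data among the methods for assessing all three. Under Data management, access to SystmONE is restricted: "Only data relevant to the study (i.e. the data specified in Table 2) will be accessed".

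Table 2, titled "Registration data to be collected by SystmONE", includes consultation date, age, ethnicity, gender, staff group, a yes/no field for whether the patient was asked, and a reason field coded "Not appropriate/time/clinician personal beliefs/other (free text".

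The Prompted choice section describes several ways out of the prompt:

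- Pressing No is recorded: "They will then be instructed to complete the following questionnaire which records reason why the patient was not asked".
- A change of plan during the consultation can also be recorded, since "question f. was included in both the ‘Yes’ and ‘No’ questionnaire".
- Staff may press Pause and resume later.
- Staff are told "Please do not press the red x", so closing the prompt is possible.
- The capacity question has the answer "No (Staff member will be unable to complete the questionnaire if they answer no to this question".

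The Discussion says that the lack of incentive "may decrease the likelihood of staff completing the intervention form, including the elements concerning feasibility (e.g. reasons for not asking patients" and looks to focus groups and online surveys to examine the effect. Quantitative analyses plans descriptive summaries of patients asked and not asked, registration rates, and differences by staff group.

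**The concern.** Prompted choice is the main intervention element, so the basic quantitative fidelity question is this: of the consultations in which a trained clinician was due to be prompted for an eligible adult, in how many was the patient asked? The numerator is in Table 2. The denominator is not, and the access rule leaves no room to fetch it from SystmONE.

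The article itself expects forms to go uncompleted. Time pressure is the barrier under study, and a clinician short of time is a plausible candidate both for not asking and for not recording. A share computed among completed forms could then look better than actual delivery. Staff groups that differ in how often they complete forms could not be compared fairly. The study is meant to show whether general practice can host the intervention and to inform a cluster randomised feasibility trial, so an unknown delivery rate would carry forward.

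**Working it through.** **1. Is there a usable denominator elsewhere in the article?** The only candidate is the forecast of about 10,000 consultations (Participant timeline, sample size and recruitment). Study setting gives about 1000 consultations a week, and the period 5 April to 9 July 2018 is 96 days.

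- 12 weeks: 12 × 1000 = 12,000
- 13 weeks: 13 × 1000 = 13,000
- exact dates: 96 / 7 × 1000 = 13,714
- 68 weekdays: 68 / 5 × 1000 = 13,600

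None reproduces 10,000, which would fit 10 weeks. The article calls the figure approximate and dependent on staffing, so this is a loose forecast and not a demonstrated error. It also counts all consultations, not those of adults seen by trained staff with the prompt still active. Prompts switch off after several responses, so the eligible number falls over the period. The forecast cannot serve as the denominator.

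**2. Which outcomes of a prompt have a place in Table 2?**

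| What happens | Field in Table 2 |
|---|---|
| Yes form, patient asked | yes |
| Yes form, patient then not asked | yes, with reason |
| No form | yes, with reason |
| Prompt closed | none |
| Prompt paused, never resumed | none |
| Form left blank | none |
| Capacity answered No | none (patient is ineligible) |

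**3. What does the gap do to a delivery rate?** Let c be the share of eligible consultations with a completed form, a the share asked among those, and u the share asked among the rest. Then

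recorded rate = a; true rate = c × a + (1 − c) × u.

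The article gives none of the three. All values below are assumptions, with a = 0.20:

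| c | u | True rate |
|---|---|---|
| 0.9 | 0 | 0.18 |
| 0.7 | 0 | 0.14 |
| 0.5 | 0 | 0.10 |
| 0.3 | 0 | 0.06 |
| any | 0.20 | 0.20 |
| 0.7 | 0.80 | 0.14 + 0.24 = 0.38 |

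With u = 0 the recorded rate is too high by a factor 1/c. With u = a there is no bias. With u above a, because staff asked but did not record, the sign reverses.

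**4. Staff groups.** Two groups that both record 0.20, with c = 0.9 and c = 0.5 and u = 0, would truly deliver 0.18 and 0.10. The permitted data would show no difference.

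**5. Patients without capacity.** They meet the exclusion criterion and belong outside the denominator. With 2,000 asked of 10,000 prompts and 5% lacking capacity (assumed), the eligible-based rate is 2,000 / 9,500 = 0.211, against 0.200 if they are wrongly counted. Omitting them does not inflate delivery. A code is needed only so that they can be removed once eligible consultations are counted.

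**6. What the count would add.** With c known, the true rate is bounded by c × a (no unrecorded patient asked) and c × a + (1 − c) (all asked). For c = 0.7 and a = 0.20 that is 0.14 to 0.44. Without c, no such bounds can be stated.

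**The case against.** The strongest case against has five parts.

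- **Recorded non-delivery is kept.** A reader might infer that the rule confines access to completed questionnaires. It does not: it limits variables, and Table 2 includes patients recorded as not asked, with reasons. This stands. The gap concerns unrecorded prompts only.
- **System behaviour is not described.** The article does not say what SystmONE stores when a prompt is closed or not resumed, so it cannot be asserted that nothing is stored. This also stands. What can be said is that Table 2 has no field for those states.
- **The practice could supply a count.** One year of baseline registrations already comes from the practice administrator, outside Table 2, and raw SystmONE data are examined weekly. This shows that the remedy is feasible. But no consultation count is planned, and the weekly check is described as a search for prompted choice by untrained staff.
- **The article defines no delivery rate.** True, so no stated figure is wrong, and a precise fidelity measure may sit in a fuller document. The point here is narrower: the article fixes a closed data list from which such a measure could not be computed.
- **Non-completion is disclosed, and other methods address it.** Focus groups and surveys can explain why forms were skipped. They cannot count how many were, and the Discussion warns that recruitment to them may also suffer.

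**Conclusion.** The concern holds in a limited form. The permitted data contain no count of eligible consultations or prompts shown, so how often patients were asked when a prompt was due cannot be computed. Delivery and the planned asked/not-asked and staff-group comparisons describe completed forms only.

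A reader might go further and conclude that delivery will be overstated. The documents do not support that as a certainty. It requires unrecorded patients to have been asked less often than recorded ones. That is plausible where time is short, but the bias vanishes if they were asked equally often and reverses if staff asked without recording. Nor do patients without capacity contribute to it, since they are ineligible.

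The size is unknown, because the article gives no completion or asking rate. In the worst case, with no unrecorded patient asked, the recorded share is too high by a factor of one over the completion fraction. For a descriptive single-practice study this is an inexpensive improvement that lets it answer its own fidelity question. It does not invalidate the design.

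**What to change.** Add to Table 2 an aggregate count for 5 April to 9 July 2018, extracted from SystmONE or supplied by the practice, of consultations with trained staff by patients aged 18 or over whose prompt was still active. Break it down by staff group and, where the system allows, by week, age band and sex. Make lack of capacity a saved code, so that these patients can be taken out of the denominator.

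Then report two figures side by side:

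- fidelity: consultations with the patient asked / eligible consultations;
- form completion: any Yes or No form / eligible consultations.

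State that patients asked but not recorded make the first figure a lower bound.

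The cost is one aggregate report and one code. The count fits the Consent section, which already allows consultation-level feasibility data not tied to the patient. The article does not establish that SystmONE can count active prompts, so this should be confirmed with the practice first. The reported delivery rate will probably be lower than the share among completed forms.
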